### Blinding

At baseline, before randomisation the measurements will be performed by the treating therapists and psychologist of the staff. The measurements at T1 and T2 will be performed by an independent trained rater. The patients are aware of the treatment they receive, so it is not possible to blind them. The rater however will be blinded for the treatment allocation: patients will be asked by the rater not to reveal the treatment to which they were assigned. A blinding check will be performed after each of the two measurement sessions (T1 and T2). A process measure as to success of rater's blinding is the rater's opinion about the group he thinks a patient belonged to.

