**Methods:**

A randomised, controlled, observer masked prospective trial will be conducted with adult stroke patients in the (sub)acute phase of stroke recovery. Over a six weeks intervention period the control group will receive multi professional therapy as usual. Patients in the experimental group will be instructed how to perform mental practice, and will receive care as usual in which mental practice is embedded in physical, occupation and speech therapy sessions. Outcome will be assessed at six weeks and six months. The primary outcome measure is the patient-perceived effect on performance of daily activities as assessed by an 11-point Likert Scale. Secondary outcomes are: Motricity Index, Nine Hole Peg Test, Barthel Index, Timed up and Go, 10 metres walking test, Rivermead Mobility Index. A sample size of the patients group and all therapists will be interviewed on their opinion of the experimental program to assess feasibility. All patients are asked to keep a log to determine unguided training intensity.

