### Background work

A full systematic review of previous evaluative research on mental practice was completed and has been published [13]. It showed some evidence suggesting that mental practice in stroke rehabilitation might work. However, the evidence still is weak. Furthermore, there is no consistency about or clarity on:

- the nature of the intervention itself (what was actually done?)

- the timing after stroke (when should patients be given mental practice?)

- control (what should be the control intervention?)

Consequently, we felt it important to set up a larger study. The review also highlighted several important issues to be considered in that:

- knowing what patients are doing during imagery [15],

- knowing whether patients are using mental practice [15],

- knowing what mental images of a movement the patient had [16],

- defining the core of mental practice [17],

- determining practicality in the commonest stroke rehabilitation setting (nursing homes in the Netherlands),

- determining what features predict success or failure.

These issues will be discussed also in this article.

A multi-centre, prospective, parallel-group, randomized, controlled, observer masked trial (RCT) will be conducted over a two year period (mid 2007-mid 2009) involving clinically diagnosed adult stroke patients, complying with all normal research governance procedures.

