### Main study parameter/endpoint

It is hypothesised that mental practice has the most effects on the movement that is actually mentally rehearsed [9,18,25,26]. Improvement of these activities should therefore be assessed. To measure if mental practice improves the performance of activities in the experimental group more than in the control group, an 11-point Likert scale will be used:

▪11 point Likert scale assesses the performance of the activities 'drinking' and 'walking' ranging from 10 ('excellent') to 0 ('poor') as perceived by the patient and the therapist. The physiotherapist and the occupational therapist will each score another task, which may be individually chosen and scored on the 11 point Likert scale. If the participant is treated for swallowing problems and/or motor problems due to a facial paresis by a speech therapist, he himself and the speech therapist will score motor actions within these two domains on perceived performance.

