Caregivers who were made enthusiastic about a new approach and have just spend a lot of time learning how to use mental practice as an additional tool may be tempted to use it as much as possible, whenever possible. This could decrease the differences between the two compared interventions. There is some evidence that altering professional behaviour is not very easy [45]. Therapists will probably need more effort to consciously implement mental practice into their daily routines then copying them in the control group. Nonetheless, therapists will undergo an integrity check too, determining how well they were able to distinguish between the two interventions in therapy. During an interview, therapists will be asked to which extend they were able to stick to the intervention contents (subjective opinion). Furthermore, the external expert will attend therapy sessions of all therapists unannounced and at random throughout the two year trial period. With these measures, we will try to maximize the contrast between the compared interventions. In case contamination does take place, we will report it as fair as possible.

From the patient's point of view, we believe there is a big difference between telling patients to imagine movements and actually teaching it. It is more probable that patients that were taught will successfully use mental practice on a regular basis. A big part of the effect will probably come from the practice outside of therapy, unguided.

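### The protocol gives the T1 and T2 measurements to a masked rater but also has the primary scale scored by the therapist, and does not settle which score is primary

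*Protocol article*

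**What the plan says.** All references are to the protocol article.

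- **Label.** The abstract (Methods) says: "A randomised, controlled, observer masked prospective trial will be conducted with adult stroke patients". Background work repeats the observer-masked description. Neither limits it to particular outcomes.
- **Who measures.** Blinding assigns baseline measurement to the treating therapists and the staff psychologist, before randomisation. For follow-up it says: "The measurements at T1 and T2 will be performed by an independent trained rater". The rater is blinded to allocation, and the section says openly that patients cannot be.
- **Who scores the primary scale.** Main study parameter/endpoint has drinking and walking scored "as perceived by the patient and the therapist". It adds: "The physiotherapist and the occupational therapist will each score another task". For patients treated for swallowing or facial motor problems, "he himself and the speech therapist will score motor actions within these two domains on perceived performance".
- **When.** Table 1 lists both primary Likert rows (drinking and walking; patient-specific tasks) at T0, T1 and T2.
- **Which score is primary.** The abstract says: "The primary outcome measure is the patient-perceived effect on performance of daily activities as assessed by an 11-point Likert Scale". Outcome measurement, in the Discussion, gives the therapist's and the patient's views equal importance when it justifies the primary scale. Sample size calculation refers to perceived improvement without saying who perceives it.

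**The concern.** A therapist who scores a patient at T1 or T2 after treating that patient cannot also be the independent masked rater. The endpoint section and the Blinding section therefore cannot both hold for the therapist score as written.

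The conflict concerns the outcome that carries the trial's conclusion. The scale is a subjective 0–10 judgement of performance, and someone who knows which treatment was given can shift such a judgement without intending to. If the therapist score counts towards the primary, a positive result could rest partly on unmasked ratings by the people who gave the treatment, in a trial described as observer masked. Because the document also differs on whether the therapist score is primary at all, the choice could be made after the scores are seen.

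**Working it through.** The main check is a comparison of passages, since no figure in the protocol is in dispute.

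**1. Do the scoring therapists know the allocation?** The endpoint section ties scoring to treating explicitly only for the speech therapist. For the physiotherapist and occupational therapist it follows from two other sections:
- Treatment of participants says that mental practice is embedded in therapy sessions by instructed paramedical therapists.
- Incorporation into routine working practice says that the trained therapists give both interventions, and that physiotherapy, occupational and speech therapy sessions of the experimental group are recorded in one central log.

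A therapist treating a trial patient therefore knows the arm.

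**2. Can the passages be read together?** There are three possible readings.

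| Reading | Consequence |
|---|---|
| Patient and treating therapist both score at T1 and T2, and both are primary | Blinding is wrong for the therapist part of the primary |
| The masked rater takes over the therapist's scoring at T1 and T2 | No contradiction, but no section describes it, and the observer changes after T0 |
| Only the patient's score is primary, as in the abstract | The primary is unmasked, as disclosed; the therapist score is outside it; the endpoint section and Outcome measurement need rewording |

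No section says which reading applies.

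**3. How much could an unmasked score matter? (illustration)**

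Inputs:
- SD 2.25, from Sample size calculation (itself the protocol's assumption).
- 35 per arm, the target in the same section. It also applies if drop-outs are kept by carrying the last measurement forward, as Multivariate analysis plans.
- 28 per arm = 35 × (1 − 0.20), using the 20% drop-out in Withdrawal of individual participants.
- Two-sided 5% test and no true effect.
- A shift *b* in the mean score due to knowledge of allocation. This is an assumption; the document gives no value.

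Formulae: SE = 2.25 × √(2/n), and P(significant) = Φ(b/SE − 1.96) + Φ(−b/SE − 1.96).

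- n = 28: SE = 2.25 × √(2/28) = 0.601
  - b = 0.5: b/SE = 0.83, so P = Φ(−1.13) + Φ(−2.79) = 13.2%
  - b = 1.0: b/SE = 1.66, so P = Φ(−0.30) + Φ(−3.62) = 38.3%
- n = 35: SE = 2.25 × √(2/35) = 0.538
  - b = 0.5: b/SE = 0.93, so P = Φ(−1.03) + Φ(−2.89) = 15.3%
  - b = 1.0: b/SE = 1.86, so P = Φ(−0.10) + Φ(−3.82) = 46.0%

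With the t distribution the figures are 12.9% and 37.2% for 28 per arm, and about 15% and 45% for 35 per arm. Both shifts are less than half of the 2.2-point difference that the trial is planned to detect.

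**The case against.** The best defence is that the document does not establish that treating therapists score the primary at follow-up. Blinding separates T0 (treating therapists) from T1 and T2 (independent rater), and the endpoint section does not say who scores at which visit. By T2 the six-week programme is over and the patient may be at home. The abstract names a patient-perceived primary, and on that reading the therapist score is not primary. This stands in part: the defect is that the document leaves the matter open, not that it commits to therapist scoring at every visit. It does not remove the defect, because the endpoint section names the therapist without exception and Table 1 schedules the scale at all three visits.

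Several stronger readings are tempting but are not supported:

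- A reader might infer that the **patient's score** also contradicts the masking. It does not. Patient unblinding is disclosed, a masked rater can collect a patient's own score, and observer masking makes no claim about patients.
- A reader might infer that therapist ratings make up a **fixed share**, such as half, of the primary. No weights or rule for combining the scores are given.
- A reader might cite "Caregivers who were made enthusiastic about a new approach" as evidence of **biased scoring**. That passage concerns contamination of the control arm, which would shrink the contrast, and says nothing about scoring.
- A reader might conclude that a positive primary should count only if a **masked test agrees**. That would be a new success criterion. The 10-metre walk is for independent walkers, and swallowing, facial movement and many individually chosen tasks have no matching test.

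The error rates in the illustration rest on an assumed shift, and the same arithmetic would apply to any unmasked score.

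**Conclusion.** The point holds for the therapist score. The protocol assigns T1 and T2 measurement to a blinded independent rater without exception, yet has its primary scale scored by the patient and the therapist, and the therapists deliver the allocated treatment. It also disagrees with itself on whether the therapist score is primary. As written, an unmasked treating-therapist rating can enter the primary result of a trial labelled observer masked.

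The size of any bias cannot be derived from the document. On the assumptions shown, a shift of 0.5 point would raise the false-positive rate from 5% to about 13–15%, and a shift of 1.0 point to about 37–46%. This is worth correcting because it concerns the endpoint that carries the conclusion and the correction is cheap.

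**What to change.** Reconcile the abstract, Main study parameter/endpoint, Blinding and Outcome measurement as follows:

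1. Make the patient's own 11-point score, collected by the independent rater at T1 and T2, the sole primary outcome. This agrees with the abstract.
2. Report the treating-therapist score as unmasked supportive data. Alternatively, have the existing masked rater give the observer score for those tasks that can be shown at the visit.
3. State that the patient-rated primary is unmasked and that observer masking covers only the outcomes the rater assesses.

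**Cost.** Mostly wording. The therapist's view no longer counts towards the primary, which gives up the equal standing that the Discussion assigns to it. Any scoring by the rater adds a little visit time to the stated extra load of about 20 minutes per assessment, because the rater has to see the tasks performed.

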### Withdrawal of individual participants

Participants can leave the study at any time for any reason if they wish to do so without any consequences. If reasons are given they will be recorded. The investigator can decide to withdraw a subject from the study for urgent medical reasons. We allowed for a 20% drop out in the size calculation.

### Follow-up of participants withdrawn from treatment

The statistical analyses will be performed according to the 'intention-to-treat' principle (patients will be analysed in the treatment group to which they were randomly assigned). Patients who withdraw from treatment but allow further data collection will have data collected.

### Statistical analysis

#### Descriptive statistics

All data will be collected on paper and the records will be stored by registration number in a secure cabinet. Anonymised data will be transferred to a computer database and secured using a password. Entries in the patients' diaries and results from the interviews will be analysed qualitatively.

### Multivariate analysis

The baseline scores of the patient's demographic, primary and secondary outcomes will be used to compare the two groups. If necessary, adjustments for baseline variables will be made, using analysis of covariance. Differences at baseline and differences between the two groups on the various assessment times will be calculated. Data will be analysed using MAN(C)OVA and Generalized Estimating Equations (GEE) analyses to ascertain the effects of mental practice based therapy on different levels of outcome and to follow improvements individually in time. Regression analyses will be used to identify prognostic variables. The statistical analysis concerned with comparing the two groups will be performed according to the 'intention-to-treat' principle (patients will be analysed in the treatment group to which they were randomly assigned). Missing data will be replaced by a linear interpolation method for missing measurements. A 'last measurement carried forward' method is used to predict outcome in dropouts [44].

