### Study population

Seventy stroke patients will be recruited in two nursing homes by the treating physicians or other staff. There are no data available concerning ability to benefit from mental practice, and so only practical factors affect inclusion and exclusion – can the person give consent and understand the instructions?

Patients entering the RCT have to meet following inclusion criteria:

a) Clinically diagnosed adult stroke patient. In nursing homes, most of the stroke patients will be elder (> 60 years old);

b) Sufficient cognitive level and communication skills to engage in mental practice; this is a clinical judgement. Patients need to be able to follow simple instructions;

c) Between two and 10 weeks of stroke onset.

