### Study parameters/endpoints

Measurement dates are at entry in the study (T0 – baseline), after a six weeks intervention period (T1) and six months after entry (T2). Additional information during the course of rehabilitation will be collected, e.g. recurrence of stroke, other intercurrent medical problems, amount of therapy received, used medication. In addition, any deviation from the treatment protocol and any co-intervention during the six months will be recorded.

In the choice of measuring instruments following considerations were taken into account.

• The measuring instruments should have sufficient methodological quality and feasibility recorded in literature and/or be recommended by the National (Dutch) stroke Guidelines;

• If possible, the measuring instrument should be part of the standard assessment in the nursing homes to restrict the additional load on the patient;

• If the quality of a listed measuring instrument has not yet been established the measuring instruments should have evidence from other studies on their potential use in stroke rehabilitation;

• The feasibility will be measured by using semi-structured interviews (process evaluation), recording co-interventions, analysing logs and monitoring therapy content in the experimental group.

The extra load for the participants due to additional clinical testing is approximately 20 minutes at each assessment point.

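### Carrying the last score forward and interpolating a missing T1 in recovering stroke patients dilutes a real effect and, if drop-out differs between arms, can create a false one

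*Protocol article*

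**What the plan says.** The Multivariate analysis section of the protocol article gives two rules for missing values. For missing measurements: "Missing data will be replaced by a linear interpolation method for missing measurements". For patients who leave: "A 'last measurement carried forward' method is used to predict outcome in dropouts". The same paragraph plans the comparison: "Data will be analysed using MAN(C)OVA and Generalized Estimating Equations (GEE) analyses", by intention to treat, so that "patients will be analysed in the treatment group to which they were randomly assigned". It names no alternative treatment of missing data and no sensitivity analysis for this choice.

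Three other parts of the article bear on the point:

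- Study population sets entry as "Between two and 10 weeks of stroke onset".
- Study parameters/endpoints gives three measurement times only: entry (T0), six weeks (T1) and six months (T2).
- Withdrawal of individual participants states the expected loss: "We allowed for a 20% drop out in the size calculation". The next section adds that patients who stop treatment but agree to further measurement will still be measured.

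**The concern.** These patients are in the phase in which recovery is expected in both arms; the article's own discussion of patient selection speaks of each person's recovery trajectory. A rule that holds a score still therefore describes an outcome that few patients would have had.

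Under LOCF, a patient lost before T1 keeps the baseline score at T1 and T2, with no recovery and no treatment effect. A patient lost after T1 keeps the six-week score. With three visits, interpolation can apply only to a missing T1 when T2 is present, and it places T1 on a straight line between T0 and T2. T1 is the end-of-treatment assessment, so any early recovery or early effect is flattened.

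Both rules feed the comparison of the two groups. The Sample size calculation section says that failure to find added value in 70 patients should put the clinical relevance of the therapy in question. A rule that dilutes a real effect pushes towards that conclusion. If drop-out differs between arms, the error can go either way.

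**Working it through.** **From the document.** 35 per arm, target difference 2.2, SD 2.25, two-sided 5% level, 20% drop-out, visits at 0, 6 and about 26 weeks. The stated drop-out is 0.20 × 35 = 7 patients per arm.

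**Assumed, because the article gives none of these.** Natural gain G of 1 to 3 points, reached by T1 and held to T2; the same treatment effect at T1 and T2; correlation 0.5 between visits; loss at random within arm; the split of drop-out between arms and its timing. Scores are treated as normal, without the 0 and 10 limits.

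**Expected LOCF estimate at T2.** Let d be the true difference, p_E and p_C the drop-out proportions in the experimental and control arms, and e the share of drop-outs who leave before T1:

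estimate = (1 − e·p_E)·d − e·(p_E − p_C)·G

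- 20%/20%, d = 2.2, all early: 0.80 × 2.2 = 1.76. Half early: 0.90 × 2.2 = 1.98.
- 20%/20%, d = 0: exactly 0, whatever G is.
- 10%/30% (control/experimental), d = 0, all early: −0.20 × G, that is −0.2 to −0.6. The largest value is 0.6/2.2 = 27% of the target. Half early: −0.10 × G, that is −0.1 to −0.3. Reversing the imbalance reverses the sign.

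**Rejection rates by simulation, G from 1 to 3.**

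| Scenario | Timing | t-test | ANCOVA |
|---|---|---|---|
| d = 2.2, 20%/20% (power) | all before T1 | about 72–84% | about 83–95% |
| d = 2.2, 20%/20% (power) | half before T1 | about 88–92% | about 94–98% |
| d = 0, 10%/30% (type I error) | all before T1 | about 6–16% | about 8–21% |
| d = 0, 10%/30% (type I error) | half before T1 | about 6–9% over both tests | |

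The t-test on observed data has about 95% power at 20%/20%. A milder imbalance matters less: with 15% v 25%, G = 2 and all losses early, the t-test type I error is 6.2%.

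**A second set-up, in which recovery continues after T1** (gain 2 at T1 and 3 at T2, correlation 0.6, ANCOVA at T2). Patients lost after T1 now miss the last point of recovery too.

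- d = 0, 10%/30%: the false difference is −0.20 × 3 = −0.60 if all leave early (rejection 23%). If half do, it is −0.20 × (0.5 × 3 + 0.5 × 1) = −0.40 (13%). Analysis of observed data rejects in 5–6% in every pattern.
- d = 2.2, 20%/20%, all early: estimate 1.76, 95% interval coverage 0.88, power 0.84 against 0.99 on observed data.
- d = 2.2, 10%/30%, all early: estimate 0.93, coverage 0.45. With 30%/10%: estimate 2.57, coverage 0.89. LOCF is therefore not reliably conservative.

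**Standard error under LOCF.** In the first set-up with 20%/20%, d = 2.2, G = 3 and all losses early, the mean reported standard error is 0.671 and the actual sampling SD 0.677. They agree.

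**Interpolated T1 (second set-up).** On calendar time the filled-in value credits 6/26 = 23% of the T0–T2 change; by visit order, 50%. The article does not say which.

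- d = 2.2, T1 missing in 20%/20%: 0.8 × 2.2 + 0.2 × 0.23 × 2.2 = 1.86 on calendar time (simulated 1.87, coverage 0.89), or 1.98 by visit order (simulated 1.99, coverage 0.92).
- d = 0, T1 missing in 10%/30%: 0.20 × (0.23 × 3 − 2) = −0.26 on calendar time (rejection 10%), or 0.20 × (0.5 × 3 − 2) = −0.10 by visit order (6%).
- d = 0, T1 missing in 20%/20%: reported standard error 0.40 to 0.41, against 0.43 with no data missing at all.

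**The case against.** Several fair points can be made on the other side, and most of them stand as limits on the size of the problem.

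- **Timing.** The largest figures assume that every drop-out leaves before T1. If half do, attenuation is mild (1.98) and the type I error in the first set-up is at most about 9%. This stands, so the results are given as ranges.
- **Assumed gain and imbalance.** Neither is in the article. Unequal loss is plausible, because only one arm takes on the imagery task, but it is not shown. Patients who stop treatment may still be measured, so abandoning the task does not always mean missing data.
- **Standard error under LOCF.** A reader might infer that both fill-ins understate the standard error. The check does not support that for LOCF, whose reported standard error matches its sampling SD. Its fault is bias, and hence intervals that cover the truth too seldom. Only interpolation can give a standard error below that of complete data.
- **Bias in every case.** A reader might also infer that LOCF always distorts the comparison. With equal drop-out and no effect it does not.
- **GEE as a ready answer.** It is tempting to say that the planned GEE simply makes filling in unnecessary. Unweighted GEE on incomplete records needs data missing completely at random, or depending only on covariates in the model.

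The objection does not remove the point itself. The article states both rules for the main comparison, so this is not detail left to an analysis plan, and nothing in the article limits their effect.

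**Conclusion.** The point holds in a bounded form. LOCF attenuates a real difference when drop-out is equal: 2.2 falls to 1.76 with 20% loss before T1, and to about 1.98 if half of that loss comes later. With unequal drop-out it can create a false difference in either direction: 0.2 to 0.6 points at 10% v 30% if all leave early, or 0.1 to 0.3 if half do, when the natural gain is 1 to 3 points and complete by T1. Continued recovery after T1 makes the half-early case worse. Interpolation is narrower in reach, depends on an unstated time scale, and can make the result look more precise than complete data would.

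The direction follows from carrying scores forward while patients recover. The sizes rest on the assumed gain, correlation, imbalance and timing. The documents do not support the reading that the rule by itself decides the trial's answer. Severity: should be fixed.

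**What to change.** In Multivariate analysis, delete both single-imputation rules for the group comparison and replace them as follows.

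1. Use all observed T0, T1 and T2 scores, as randomised, in a likelihood-based mixed model for repeated measures with group, time, group-by-time and the T0 score. Alternatively, use GEE after multiple imputation. If unweighted GEE is run on incomplete records, state the stronger missingness assumption it needs.
2. State that scores collected after withdrawal from treatment are included.
3. Add a sensitivity analysis for data not missing at random, such as a delta adjustment applied separately by arm.
4. Keep LOCF at most as a labelled sensitivity analysis.

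The cost is a change of wording and slightly more programming, with no new data, visits or patients. The main analysis would then rest on a missing-at-random assumption, which item 3 is there to test.
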